## Abstract

Background: The increasing use of immune checkpoint inhibitors (ICIs) in the treatment of both advanced and early stages of various malignancies has resulted in a substantial increase in the incidence of cardiovascular (CV) immune-related adverse events (irAEs). The current follow-up guidelines are based on anecdotal evidence and expert opinions, due to a lack of solid data and prospective studies. As many questions remain unanswered, cardiac monitoring, in patients receiving ICIs, is not always implemented by oncologists. Hence, an urgent need to investigate the possible short- and long-term CV effects of ICIs, as ICI approval is continuing to expand to the (neo)adjuvant setting. Methods: We have initiated a prospective, multicenter study, i.e., the CAVACI trial, in which a minimum of 276 patients with a solid tumor, eligible for ICI treatment, will be enrolled. The study consists of routine investigations of blood parameters (troponin and N-terminal pro-B-type natriuretic peptide (NT-proBNP) levels, in particular) and a thorough CV follow-up (electrocardiograms, transthoracic echocardiograms, and coronary calcium scoring) at fixed time points for a total period of two years. The primary endpoint is the cumulative incidence of troponin elevation in the first three months of ICI treatment, compared to baseline levels. Furthermore, secondary endpoints include incidence above the upper limit of normal of both troponin and NT-proBNP levels, evolution in troponin and NT-proBNP levels, the incidence of CV abnormalities/major adverse cardiac events, evaluation of associations between patient characteristics/biochemical parameters and CV events, transthoracic echocardiography parameters, electrocardiography parameters, and progression of coronary atherosclerosis. Recruitment of patients started in January 2022. Enrolment is ongoing in AZ Maria Middelares, Antwerp University Hospital, AZ Sint-Vincentius Deinze, and AZ Sint-Elisabeth Zottegem. Trial registration: ClinicalTrials.gov Identifier: NCT05699915, registered 26 January 2023.

## 1. Introduction

Immune checkpoint inhibitors (ICIs) have significantly altered the field of oncology during the last decade by improving clinical outcomes in multiple cancer types. Currently, the U.S. Food and Drug Administration (FDA) has approved eight ICIs for over 50 indications. Nevertheless, the increasing use of ICIs in the treatment of both advanced and early stages of various malignancies has resulted in a substantial increase in immune-related adverse events (irAEs). The most frequently observed irAEs occur in the skin, endocrine system, and gastrointestinal tract. The majority of irAEs can be managed effectively if found and treated early. Other irAEs, i.e., myocarditis, pneumonitis, encephalitis, and hepatitis, are less frequently seen, though can be potentially fatal.

More specifically, immune-related cardiovascular (CV) events (myocarditis, pericardial disease, peri myocarditis, vasculitis, left ventricular dysfunction, acute coronary syndromes, and arrhythmias and cardiac conduction abnormalities) have gained significant interest over the last few years due to their high mortality rate e.g., ICI-induced myocarditis (39.7 to 50%) [1,2,3,4,5,6,7,8,9,10,11]. Moreover, there is increasing evidence that cardiac irAEs have been missed in a non-negligible number of patients during the initial years of ICI approvement, due to the wide varieties of clinical presentation [12]. Furthermore, the lack of routine monitoring for cardiac events and the inclusion of a highly-selected and healthier patient population in immunotherapy trials has most likely contributed to the under-reporting of CV irAEs. As ICIs evolve to include high-risk patients with pre-existing CV risk factors and disease, as well as patients receiving ICIs in the adjuvant setting, the risk of ICI-induced cardiotoxicities is highly relevant.

A recent systematic review and meta-analysis of 125 trials, which included 20,218 patients treated with either anti-programmed cell death protein-1 (PD-1) or anti-programmed cell death ligand-1 (PD-L1), revealed 82 treatment-related deaths. Importantly, of these 82 deaths, there was a 9.8% incidence of CV death, including myocardial infarction and acute coronary syndromes. The important role of cytotoxic T-lymphocyte-associated antigen-4 (CTLA-4) has already been suggested 25 years ago in a CTLA-4 deficient mouse strain with the development of lymphoproliferative disease with multiorgan lymphocytic infiltration and tissue destruction, with particularly severe myocarditis and pancreatitis, and death after 3–4 weeks of age. Recently, in patients treated with ICIs for melanoma, a significantly increased uptake of 2-[18F]fluorodeoxyglucose in the large arteries was observed which could indicate vascular inflammation. Vascular inflammation is a well-known contributor to atherosclerosis and heart failure with preserved ejection fraction. Accordingly, recent clinical data has shown a three-fold higher risk of CV events after ICI initiation, as well as a three-fold higher rate of progression of total aortic plaque volume, thus suggesting that CV irAEs could be mediated by an accelerated progression of atherosclerosis [8,13,14,15,16,17,18,19,20,21,22,23,24,25,26].

Several international guidelines recommend preventive/screening measures for CV irAEs as a safety margin. More specifically, the current guidelines (NCCN, ASCO, ESC, and SITC) recommend an electrocardiogram (ECG) and a CV risk assessment in all patients prior to ICI initiation [6,9,27,28,29,30,31,32,33]. Baseline echocardiography is only recommended in high-risk patients (dual ICI therapy, combination of ICI therapy with other cardiotoxic therapies, prior cancer therapy-related cardiac dysfunction, or prior CV disease), however, it can be considered in all patients (level C evidence) [33]. In addition, they also recommend the baseline determination of cardiac markers in all patients, i.e., troponin and brain natriuretic peptide (BNP), or its prohormone N-terminal pro-B-type natriuretic peptide (NT-proBNP). As cardiac irAEs often tend to occur during the first three months of treatment, most guidelines also recommend serial troponin measurements prior to each cycle during the first weeks of treatment, especially in patients with an abnormal baseline value [1,6,9,29,31,34,35,36].

Cardiac markers such as high-sensitivity troponin I/T (hs-TnI/hs-TnT), BNP, and NT-proBNP are crucial in the diagnosis of CV diseases. For example, troponin is a well-known cardiac biomarker that has become indispensable in the diagnosis of acute coronary syndromes. However, its role in cardio-oncology, more specifically in the active surveillance of ICI-mediated CV events, is not clear. Hence, the current guidelines are based on anecdotal evidence and expert opinions, due to the lack of solid data and prospective studies [33,37]. Therefore, cardiac monitoring, in patients receiving ICIs, is not always implemented by oncologists, as many questions remain unanswered:How should hs-TnI/hs-TnT levels be graded? The Common Terminology Criteria for Adverse Events (CTCAE, Version 5) is widely accepted as the standard classification and severity grading scale for adverse events in cancer therapy, clinical trials, and other oncology settings [38]. However, the current grading system makes it challenging to accurately document and report the severity and incidence of increased cardiac troponins, leading to ICI-induced CV toxicity. Furthermore, BNP and NT-proBNP are not even listed in the current CTCAE criteria.What are the cut-off values for cardiac markers for clinically meaningful changes in ICI-treated patients? When do further investigations need to be performed? (The upper limit of normal (ULN) is determined on a healthy patient population).What is the appropriate time interval between the testing of cardiac markers?What is the appropriate monitoring duration of cardiac markers? Three months or longer?

Our narrative review summarized previously conducted research regarding troponin levels in patients receiving ICI [39]. As prospective data are lacking, we initiated a multicenter, prospective trial (NCT05699915) in which patients with a solid tumor eligible for ICI treatment, i.e., anti-CTLA-4, anti-PD-1, and/or anti-PD-L1, will be enrolled. Patients receiving concurrent systemic antineoplastic treatment will be excluded in order to have a homogeneous treatment population. The patients included in this study will receive a thorough CV work-up at baseline and at regular time points during treatment for a total period of two years. Our aim is to study cardiac markers in patients receiving ICI therapy and to explore the association between CV abnormalities and major adverse cardiac events (MACEs).

## 2. Methods and Analysis

### 2.1. Study Flow

The CAVACI trial, i.e., extensive CArdioVAscular characterization and follow-up of patients receiving immune checkpoint inhibitors, is a prospective, multicenter study. The study was approved by the central ethics committee of the Antwerp University Hospital (2021–1908, 2022–1908) and follows the standards of the Declaration of Helsinki and the ethical standards of the responsible committee on human experimentation. The study consists of routine investigations of biochemical parameters and a thorough CV follow-up at fixed time points. Patients included in the study will be followed for a total period of two years (Figure 1). Patients are currently being recruited via the multidisciplinary oncology board of each hospital. As of January 2022, 57 patients were enrolled.

### 2.2. Participants

#### 2.2.1. Inclusion Criteria

All patients must fulfill the following inclusion criteria:At least 18 years of age, at the time of giving informed consent.Able to provide informed consent.Have a solid tumor and will receive one of the following FDA-approved therapies, i.e., anti-PD-1, anti-PD-L1, and/or anti-CTLA-4 therapy in mono- or combination therapy.Have to be literate in Dutch or English.

#### 2.2.2. Exclusion Criteria

Prior treatment with immunotherapy (ICIs, T-cell transfer therapy, cancer treatment vaccines, or immune system modulators).Receive a regimen where ICIs will be administered together with other systemic anti-cancer agents (chemotherapy, tyrosine kinase inhibitors (TKI), etc.).History of human immunodeficiency virus infection.History of hepatitis B (defined as hepatitis B surface antigen [HBsAg] reactive) or known hepatitis C virus (HCV) (defined as detectable HCV RNA via qualitative nucleic acid testing) infection.Diagnosis of immunodeficiency or receiving chronic systemic steroid therapy (in daily doses exceeding 10 mg of prednisone equivalent).

### 2.3. Schedule of Examinations

#### 2.3.1. Baseline Patient/Disease Characteristics

Upon enrolment, the following data will be collected:Informed consent.Demographics (Eastern Cooperative Oncology Group performance status, age at start of treatment, sex, body mass index).Medical history: CV risk, COVID-19, auto-immune diseases, and other medical conditions.Current oncological disease (clinical and pathological TNM classification, current disease status, prior treatment, and molecular screening profile).Prior cancer history.Prior/concomitant medication review, especially antibiotic and oral steroid use.Other relevant parameters.

#### 2.3.2. Electrocardiogram (ECG)

A standard resting 12-lead ECG will be obtained (Supplementary Table S1) using an ECG machine (GE Healthcare, Acertys, Horten, Norway) and will be analyzed for intervals, wave vectors, and morphology, ST-segment changes and corrected QT interval (QTc) using Bazett’s Formula.

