#### 2.4.2. Secondary Endpoints

The incidence of hs-TnT/NT-proBNP elevations at 6, 12, and 24 months.The incidence of hs-TnT/NT-proBNP above the ULN at baseline, 3, 6, 12, and 24 months *.Evolution of hs-TnT/NT-proBNP in 24 months compared to baseline.Evolution of transthoracic echocardiography parameters at baseline, 3, 6, 12, and 24 months *.Evolution of electrocardiography parameters at baseline, 3, 6, 12, and 24 months.*Association between the evolution of troponin/NT-proBNP and transthoracic echocardiography and electrocardiography parameters at baseline, 3, 6, 12, and 24 months *.Cumulative incidence of CV abnormalities at 3, 6, 12, and 24 months based on the CARDIOTOX classification system of Sendón et al. (Table 1), with the inclusion of pericardial effusion and new arrhythmias [41]:

**Table 1 pharmaceuticals-16-00625-t001:** Cardiovascular abnormalities will be based on the CARDIOTOX classification system of Sendón et al. [41]. We will also document pericardial effusion and new arrhythmias as cardiovascular abnormalities.

Normal	Patients with Normal Biomarkers and LV Function Parameters
Mild	Asymptomatic patients with LVEF ≥ 50% with elevated biomarkers Asymptomatic patients with LVEF ≥ 50% with at least one additional abnormal echo parameter: (1) Increased LVESV (2) LA area > 30 cm^2^ (3) 10% decrease of LVEF to an LVEF < 53% (4) Average E/e’ > 14 (5) GLS > −18% (6) 15% relative reduction of GLS from baseline
Moderate	Asymptomatic patients with LVEF ≥ 40% and <50% with or without biomarker increase or other LV function abnormalities
Severe	Patients with asymptomatic LVEF < 40% Clinical HF: - HFrEF: HF symptoms/signs and LVEF < 40% - HFmrEF: symptoms/signs of HF with elevated NT-proBNP, LVEF 40–49%, and at least one additional criteria (enlarged LA, LV hypertrophy, or other relevant diastolic function parameters) - HFpEF: in presence of symptoms/signs of HF, elevated NT-proBNP, LVEF ≥ 50%, and at least one additional criteria (enlarged LA, LV hypertrophy, or other diastolic dysfunction parameters)

Abbreviations: GLS, global longitudinal strain; HF, heart failure; HFmrEF, HF with mildly-reduced ejection fraction; HFpEF, HF with preserved ejection fraction; HFrEF, HF with reduced ejection fraction; LA, left atrial; LV, left ventricular; LVEF, left ventricular ejection fraction; LVESV, left ventricular end-systolic volume; NT-proBNP, N-terminal pro-B-type natriuretic peptide.

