Association between the evolution of troponin/NT-proBNP and CV abnormalities.Cumulative incidence of MACEs at 3, 6, 12, and 24 months. MACEs were defined as the composite outcomes of nonfatal stroke, nonfatal myocardial infarction, hospital admission for heart failure (HF), cardiac revascularization, and CV death.Overall survival *.Association between the evolution of troponin/NT-proBNP and MACEs.The difference in the evolution of hs-TnT/NT-proBNP/transthoracic echocardiography and electrocardiography parameters between combination therapy and monotherapy.Association between patient characteristics and troponin.Association between patient characteristics and NT-proBNP.Agreement between hs-TnT and hs-TnI levels at baseline, 3, 6, 12, and 24 months *.The proportion of severe immune-related non-CV toxicities (grades 3–5).Association between the evolution of troponin/NT-proBNP and severe immune-related non-CV toxicities (grade 3–5).Association between the evolution of troponin/NT-proBNP and overall survival.Association between the evolution of troponin and diastolic function (based on the recommendations of Nagueh et al. [42]).Association between the evolution of troponin and calcium score.

* These endpoints will also be evaluated in a preliminary analysis once 50 patients have reached their 3-month cardiac follow-up visit. The sample size was not adjusted for interim analysis as the release of preliminary results is not data-driven and does not affect the error structure of the trial. Study-level conclusions will only be made once the final results of the trial have been analyzed.

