### 2.6. Data Analysis

All patient data will be collected via REDCap (a Research Electronic Data Capture), a secure HIPAA (Health Information Portability and Accountability Act)-compliant Web-based application, using a standardized data collection form. Data needed for analyses will be extracted from REDCap [43,44]. For categorical variables, frequencies and percentages will be reported. Where values are missing, percentages will be calculated for the available cases, and the denominator will be mentioned. Continuous variables will be summarized as mean with standard deviation and range.

For the primary endpoint, the cumulative incidence of troponin elevation will be calculated with death as a competing risk. Cumulative incidences and corresponding 95% confidence intervals will be reported at 3, 6, 12, and 24 months and a cumulative incidence plot will be used to visualize the results.

Similarly, for the secondary endpoints elevation of NT-proBNP, CV abnormalities, and MACE, cumulative incidences and 95% confidence intervals will be calculated, considering death as a competing event.

Evolution of troponin, NT-proBNP, transthoracic echocardiographic, and electrocardiographic parameters over time will be first studied in a linear mixed effects model with a random intercept per subject to account for the correlation of measurements coming from the same individual. This model will be extended with patient and treatment characteristics and their interaction with time, to evaluate their impact on the evolution of these parameters.

The association between the longitudinal evolution of troponin levels and time-to-event endpoints (CV abnormality, MACE) will be studied in a joint model combining a linear mixed model for troponin and a sub-distributional proportional hazards model for the time-to-event taking into account death as a competing event for CV abnormality and MACE. Latent random variables and common covariates are used to link the sub-models for the longitudinal measurements with the competing risk failure time data. In this way, the association between the evolution of the longitudinal measurements and time to event can be evaluated. Furthermore, by modelling the time to event, the analysis of the longitudinal measurements is adjusted for non-ignorable missing data due to informative dropout caused by deaths.

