Agreement between hs-TnT and hs-TnI (measured in all patients at baseline, 3, 6, 12, and 24 months) will be assessed in Bland–Altman curves and intraclass correlation coefficient (ICC) based on a two-way mixed effects model. The ICC and 95% confidence interval will be reported. Statistical analyses will be performed using R Software version 4.1.2 or higher.

As our clinical trial is an exploratory trial, secondary outcomes will be treated as exploratory results. Therefore, any definite finding for secondary outcomes will require further confirmatory studies to support possible findings. Hence, it is not needed to adjust for multiple testing for multiple secondary outcomes [45].

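### QTc is fixed to Bazett's formula with no heart rate named in the ECG model, so any heart-rate shift between visits may be partly read as QTc change

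*Protocol article*

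**What the plan says.** Section 2.3.2 lists what will be read from the resting 12-lead ECG. The list includes intervals and "corrected QT interval (QTc) using Bazett’s Formula". Bazett's is the only rate correction in the document.

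QTc is therefore one of the ECG parameters that enter three secondary endpoints in Section 2.4.2:
- "Evolution of electrocardiography parameters at baseline, 3, 6, 12, and 24 months";
- the association of troponin and NT-proBNP evolution with echocardiographic and ECG parameters;
- the difference in evolution of biomarkers and of "transthoracic echocardiography and electrocardiography parameters between combination therapy and monotherapy".

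The asterisks in Section 2.4.2 appear to place the first two in the preliminary analysis at 50 patients as well.

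Section 2.6 analyses ECG parameters in a "linear mixed effects model with a random intercept per subject" and adds: "This model will be extended with patient and treatment characteristics and their interaction with time". It does not list those characteristics, and heart rate at each ECG is not named. The same section states that "secondary outcomes will be treated as exploratory results".

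**The concern.** Bazett's formula divides QT by the square root of RR. If the true relation between QT and RR in these patients has another exponent, the corrected value still depends on heart rate. A change in heart rate from one visit to the next then moves QTc with no change in repolarisation. The cohort has no untreated group from which such a movement could be subtracted, and a larger sample does not average it out.

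Three readings could be affected:
- **Trajectory.** A shift in the cohort's mean heart rate is partly read as QTc prolongation or shortening.
- **Biomarker association.** If heart rate moves in the same patients as troponin or NT-proBNP, a QTc association can arise from the correction alone.
- **Combination versus monotherapy.** A difference in heart-rate change between the groups carries into the comparison.

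Whether heart rate shifts in this cohort is not documented. The Introduction says of immune-related adverse events: "The most frequently observed irAEs occur in the skin, endocrine system, and gastrointestinal tract". It also lists myocarditis, left ventricular dysfunction and arrhythmias among the cardiovascular events. It is plausible that some of these change heart rate, but that is an assumption.

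**Working it through.** **The plan's own figures.** The article gives no figure for QTc. Its one planning calculation, 249 patients raised to 276, does not enter this point.

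**Inputs**
- From the article: Bazett's correction (Section 2.3.2); linear mixed model with no visit-level heart rate named (Section 2.6).
- Assumed: a rate-corrected QT constant at 410 ms, so that there is no true repolarisation change; a QT-RR exponent *a*, varied from 0.25 to 0.50; and the heart-rate shifts shown below.

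**Formula.** With RR = 60/HR in seconds, let QT = 410 × RR^a. Then

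Bazett QTc = QT / RR^0.5 = 410 × RR^(a − 0.5) = 410 × (HR/60)^(0.5 − a).

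This is free of HR only when a = 0.5. The artefact between two visits is the difference of this expression at the two heart rates.

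**Small shifts at a = 1/3** (power 1/6)
- 70 bpm: 410 × (70/60)^(1/6) = 420.7 ms.
- 75 bpm: 410 × (75/60)^(1/6) = 425.5 ms, a change of +4.9 ms (from unrounded values).
- 80 bpm: 410 × (80/60)^(1/6) = 430.1 ms, a change of +9.5 ms.
- 60 bpm: 410.0 ms, a change of −10.7 ms from 70 bpm.

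**Sensitivity to the exponent, 70 to 80 bpm.** The last column applies a cube-root (Fridericia) correction to the same data, 410 × (HR/60)^(1/3 − a).

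| a | Bazett artefact (ms) | Cube-root artefact (ms) |
|---|---|---|
| 0.25 | +14.5 | +4.6 |
| 0.30 | +11.4 | +1.8 |
| 1/3 | +9.5 | 0.0 |
| 0.37 | +7.3 | −2.0 |
| 0.40 | +5.6 | −3.6 |
| 0.45 | +2.8 | −6.2 |
| 0.50 | 0.0 | −8.8 |

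Two things follow. The Bazett artefact is zero only at a = 0.50. The cube-root correction has its own artefact at every exponent other than 1/3. At a = 0.25 both formulas rise (+14.5 and +4.6 ms) although nothing has changed, so agreement in direction between them does not show a real effect.

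**Which shift matters.** For the trajectory in the mixed model, the relevant quantity is the change in mean heart rate across the cohort, so steps of 5 to 10 bpm are shown. A rise from 70 to 90 bpm would give +18.0 ms at a = 1/3. That describes a single patient with a large change, and the article gives no basis for a cohort mean shift of that size.

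**The case against.** The case for leaving the plan alone has several parts.

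- **Bazett is a recognised correction, named in advance, and nothing in the article contradicts it.** This stands: choosing it is not an error. The point is that the choice leaves a dependence on heart rate which the stated model does not address.
- **The documents give no QT-RR exponent and no heart-rate data.** This also stands. A reader might infer that heart-rate changes will distort QTc in this trial. The article does not support that: if the exponent is 0.5, or if heart rate does not shift, the artefact is zero. The claim has to stay conditional.
- **A condensed article leaves covariate lists to the full plan.** This holds in part. Section 2.6 does not list its covariates, so the absence of heart rate is not by itself a finding. The fixed use of Bazett is a stated method, however, and the point rests on that.
- **The consequence is small.** This stands. QTc is one of several ECG features. It does not enter the primary endpoint, the sample size, the CARDIOTOX categories in Table 1 or the definition of MACE, and no QTc threshold is stated. Exploratory status calls for caution and confirmation, but it does not remove a systematic shift.
- **Fridericia is not a clean replacement.** This stands. A reader might infer that changing the formula, or trusting QTc results only where the two formulas agree, would settle the matter. The table shows that neither does.

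**Conclusion.** The point holds in conditional form and is minor. Section 2.3.2 fixes one rate correction, and Section 2.6 names no visit-level heart rate. If heart rate shifts between visits and the QT-RR exponent is not 0.5, part of the shift enters the three QTc-related secondary analyses as apparent QTc change.

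Assuming a rate-corrected QT of 410 ms and exponent 1/3, the artefact is about +5 ms for a 5 bpm rise from 70 bpm and about +9.5 ms for a 10 bpm rise. Over exponents from 0.50 to 0.25 the 10 bpm figure runs from 0 to +14.5 ms. Within that range of exponents, falls in heart rate give the opposite sign. A spurious biomarker association needs one more assumption, that heart rate moves with troponin or NT-proBNP, and it cannot be sized from the article.

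The other ECG parameters do not pass through this correction.

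**What to change.** For the QT endpoint, enter uncorrected QT as the outcome of the linear mixed model in Section 2.6, with RR (or heart rate) from the same ECG as a time-varying covariate. The correction is then estimated from the trial's own recordings and needs no outside exponent. Modelling log QT on log RR would match the power relation used above.

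Base conclusions on QT evolution, on its association with biomarkers and on combination versus monotherapy on that analysis. Report Bazett and Fridericia QTc as descriptive or sensitivity results, and do not treat agreement between them as evidence of a real change.

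The cost is one extra covariate and a repeat of the model. Intervals are already among the quantities read from each ECG, so QT and RR should be available and no new measurement is needed. The primary endpoint and the 276 patients stay as they are. The change is best written down before the preliminary analysis at 50 patients.
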